#### **7.7 Premature termination of the study**

The study is an observational study, describing the progression of vessel wall calcification during different accepted treatment modalities. The only reason for terminating the study prematurely is when it would become impossible to measure the primary endpoint, i.e. the coronary artery calcification score. As MSCT is a validated and safe method for measuring calcification, it would be unlikely that this would be necessary. In theory, however, it could be possible in case of severe logistical problems or when new evidence would appear about the safety of MSCT.

## **8. SAFETY REPORTING**

### **8.1 Section 10 WMO event**

In accordance to section 10, subsection 1, of the SMO, the investigator will inform the subjects and the reviewing accredited METC if anything occurs, on the basis of which it appears that the disadvantages of participation may be significantly greater than was foreseen in the research proposal. The study will be suspended pending further review by the accredited METC, except insofar as suspension would jeopardize the subjects' health. The investigator will take care that all subjects are kept informed.

### **8.2 Adverse and serious adverse events**

Adverse events are defined as any undesirable experience occurring to the patient during the study, whether or not considered related to the diagnostic procedures. All adverse events reported spontaneously by the subject or observed by the investigators will be recorded.

A serious adverse event is any untoward medical occurrence or effect that at any dose

- results in death;
- is life threatening (at the time of the event);
- requires hospitalization or prolongation of existing inpatients' hospitalization;
- results in persistent or significant disability or incapacity;
- is a congenital anomaly or birth defect;
- is a new event of the study likely to affect the safety of the subjects, such as an unexpected outcome of an adverse reaction.

As SAEs occur highly frequently in ESRD patients (such as urinary tract infections requiring hospitalization in renal transplant patients), it is infeasible to report every SAE to the METC. SAEs are reported to the accredited METC that approved the protocol according to the requirements of that METC, if a possible relationship to administration of intravenous contrast during coronary MSCT exists, and/or if SAEs occur within 48 hours of a follow-up visit or multislice CT-scan with or without intravenous contrast administration. Deaths are always reported to the accredited METC, irrespective of the conditions mentioned above.

#### **8.2.1 Suspected unexpected serious adverse reactions (SUSAR)**

Not applicable

#### **8.2.1 Annual safety report**

The annual safety report will be combined with the annual progress report (see chapter 11.3).

### **8.3 Follow-up of adverse events**

All adverse events will be followed until they have abated, or until a stable situation has been reached. Depending on the event, follow up may require additional tests or medical procedures as indicated, and/or referral to the general physician or a medical specialist.

#### **8.4 Data Safety Monitoring Board (DSMB)**

No such committee will be established, because the study is non-interventional study, and treatment is not dependent on participation in the study.

## **9. STATISTICAL ANALYSIS**

### **9.1 Descriptive statistics**

The population characteristics are described with a categorical or continuous output, as appropriate.

The primary endpoint, coronary artery calcification score, is a continuous variable with a skewed distribution, and will be presented with its median and ranges. Progression of calcification score will be analyzed with multinomial logistic regression, dividing the coronary artery calcification score in three categories. The same goes for pulse wave velocity of the aorta and iliac arteries.

The calcification score of the different groups will be compared by regression analyses.

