**Main study parameters/endpoints:**

1. Change in coronary artery calcification score, per patient;
2. Change in pulse wave velocity, per patient.

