### **4.4 Sample size calculation**

The effects of the different modalities of renal replacement therapy on arterial calcification are analyzed with linear regression, after transformation of calcium scores. The effects of risk

factors for calcification, including inflammation parameters and calcification inhibitors are analyzed in a multivariate model. The mean ( $\pm$ SD) coronary calcification score in ESRD patients is 2370 ( $\pm$  352). The multislice CT-scan is extensively validated in our institute. At this level of calcification the variation between independent measurements is less than 10%. Therefore we can demonstrate an increase or decrease in calcification score of 15%, in 4 subpopulations of 22 patients with ESRD, with a type I error probability for a two sided test of 0.05 and a power of 0.90 [formula: " $N = (2(Z_{\alpha} + Z_{\beta})^2 \cdot sd) / (0.15 \cdot \text{mean})$ " where N = number of patients per group,  $Z_{\alpha} = 1.96$ ,  $Z_{\beta} = 1.28$ ,  $S = 3.52$ , mean = 2370]. To account for a dropout of patients by renal transplantation, switch to a different treatment modality, refusal of further participation or death we intend to include 40-55 patients per group – depending on the dropout, aiming to obtain complete study data in 22 patients per group.

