## **7. METHODS**

### **7.1 Study endpoints**

#### 7.1.1 Main study endpoint

The primary endpoint of the study is:

- change in coronary artery calcification score

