### **9.2 Univariate analysis**

The relation between each independent variable (demographic data, calcium-phosphate parameters, inflammation markers and calcification inhibitors), and primary outcomes will be determined with univariate linear regression analysis. The relationship between these independent variables and secondary outcomes (change in coronary calcification score, change in pulse wave velocity) will be determined with univariate linear regression analysis. Because the relative change in calcification score can be independent from the initial absolute calcification score, the results will be corrected for initial calcification score.

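### The protocol gives two conflicting models for its primary endpoint and labels that endpoint inconsistently; the three-category model would not deliver the stated 90% power for a two-group comparison at 22 completers per group

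*Protocol*

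**What the plan says.** **Endpoint.** Section 7.1.1 has one primary endpoint, "change in coronary artery calcification score", and the Introduction agrees. Section 9.1 applies the words primary endpoint to the score, not to its change. Sections 9.2 and 9.3 refer to primary outcomes without defining them; 9.2 then names "secondary outcomes (change in coronary calcification score, change in pulse wave velocity" as secondary, and 9.3 does the same. The Summary's list of main endpoints has a second entry, "Change in pulse wave velocity, per patient", which section 7.1.2 places among the secondary endpoints.

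**Method.** Section 4.4 says that the effects of modality "are analyzed with linear regression, after transformation of calcium scores". Section 9.1 says "Progression of calcification score will be analyzed with multinomial logistic regression, dividing the coronary artery calcification score in three categories", without cut-points, and adds that the groups will be compared by regression of an unnamed kind. Sections 9.2 and 9.3 use linear regression for the risk factors, and 9.2 corrects for the initial score.

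**Size.** Section 4.4 claims that "we can demonstrate an increase or decrease in calcification score of 15" per cent in four groups of 22, "with a type I error probability for a two sided test of 0.05 and a power of 0.90".

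**The concern.** A linear model for a transformed score and a multinomial model for three categories estimate different quantities and can lead to different conclusions. With both in the protocol and no cut-points, the primary result could be chosen once the data are seen. The sample size also rests on the continuous analysis, so using the categorical one gives up power that 4.4 does not budget for.

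The labels matter because this is not a randomised study. Patients choose their modality, and the matching in 4.1 covers age, sex, diabetes and dialysis duration but not baseline calcification. A comparison of score levels can therefore reflect differences present at entry. Change in score is what the primary objective asks about.

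**Working it through.** **1. The plan's own figure.** Inputs from section 4.4: "coronary calcification score in ESRD patients is 2370", SD 352, difference 15% of the mean, two-sided alpha 0.05, power 0.90.

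- Difference: 0.15 × 2370 = 355.5. Standardised effect: 355.5 / 352 = 1.01.
- Formula as printed: 2 × (1.96 + 1.28)² × 352 / 355.5 = 20.8, so 21.
- Usual form with the ratio squared: 2 × (1.96 + 1.28)² × (352 / 355.5)² = 20.6, so 21.
- Exact two-sample t-test: power 0.891 at 21 per group and 0.905 at 22.

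The stated 22 per group is reproduced for a continuous outcome. (The formula legend prints S = 3.52, which would give 0.21 patients, so 352 must have been used. That is a separate misprint.)

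**2. The three-category model at the same size.** With one two-level factor and three categories, the multinomial model is saturated. Its likelihood-ratio test is G = 2 Σ O ln(O/E) on a 2 × 3 table with 2 degrees of freedom (critical value 5.991). Assumptions, because the protocol does not fix them: normal data, standardised effect 1.01, 22 per group, and the cut-points listed. There were 100,000 simulations per row.

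| Cut-points | Power, likelihood ratio | Power, Pearson |
|---|---|---|
| Pooled tertiles | 0.74 | 0.73 |
| Midpoint of the two means ± 0.43 SD | 0.76 | 0.75 |
| Midpoint ± 0.75 SD | 0.77 | 0.74 |
| Tertiles of the lower group | 0.75 | 0.71 |
| Higher group's mean and 1 SD above it | 0.68 | 0.60 |
| Lower group's mean and 1 SD below it | 0.69 | 0.60 |
| No categories (t-test) | 0.90 | – |

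By likelihood ratio the loss runs from 0.90 − 0.77 = 0.13 to 0.90 − 0.68 = 0.22. A test that uses the order of the categories, or only the top-versus-bottom contrast, has power 0.82 with tertiles.

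**3. Completers needed with tertiles.** Simulated power is 0.74 at 22 per group, 0.87 at 30, 0.90 at 32, 0.89 at 34 and 0.94 at 36. The curve is slightly uneven because counts are discrete, so 32 is approximate.

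**4. Overall test of four groups of 22, tertiles (40,000 simulations each).**

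- A and B differ from C and D: 0.98 for the F test, 0.90 for the multinomial test.
- One group differs from the other three: 0.94 against 0.78.

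**The case against.** The intended endpoint can be worked out. The Introduction and 7.1.1 both say change in score, section 7.7 also shortens it to the score, and the labels in 9.2 and 9.3 look like a drafting slip. That stands, but it shows how to correct the text, not that the text is consistent.

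The power loss is not a fixed property of the plan. It depends on unstated cut-points, and section 9.1 itself says that the score is skewed. In the overall four-group test with the hypothesised pattern, the multinomial model still reaches 90%. More patients may also complete: the Summary's 25% loss from 40–55 enrolled leaves 0.75 × 40 = 30 to 0.75 × 55 = 41 per group, where tertile power is about 0.87 to 0.96. All of this stands and is why a range is given. Section 4.4 nevertheless aims at 22 complete per group and claims its 90% there.

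A reader might infer more than the protocol supports:

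- *Three incompatible methods.* Sections 9.2 and 9.3 are linear, as 4.4 is, and are written for risk factors without listing modality. Their silence on transformation does not contradict 4.4. There are two conflicting model families and one unnamed regression.
- *The multinomial model is the only one tied to progression.* Section 9.2 applies linear regression to change in score.
- *Categories of the score would hardly detect progression.* The sentence in 9.1 has progression as its subject, so categories of progression are a possible reading, and without cut-points the claim cannot be tested.
- *The multinomial test inflates type I error.* With tertiles the likelihood-ratio test rejects in 5.9% of null simulations, but Pearson's test does so in 4.3%. This depends on the statistic chosen, which the protocol does not name.
- *Uncorrected pairwise tests inflate the family error.* The protocol plans no set of pairwise tests, and contrasts may be left to the statistical analysis plan.

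**Conclusion.** The point holds as a contradiction within the protocol, so it does not depend on what a statistical analysis plan may add. The sole primary endpoint has two conflicting model families, and its status differs between 7.1.1, 9.1 and 9.2–9.3. Pulse wave velocity is ranked differently in the Summary and 7.1.2.

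If section 9.1 is followed at 22 completers per group, a two-group comparison has about 74% power with tertiles instead of about 90%. This rests on normal data, a 2-degree-of-freedom test, and the plan's SD of 352. That SD describes a score measured once and here stands in for the SD of change. The size of the loss is therefore indicative; the contradiction does not rest on it.

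**What to change.** - In 9.1, name one primary analysis consistent with 4.4: linear regression of change in the transformed score on treatment modality, with baseline score as covariate, as 9.2 already intends. Let this replace the unnamed regression for the group comparison.
- Delete the multinomial model, or keep it as a sensitivity analysis with cut-points fixed before the data are seen.
- Correct 9.1–9.3 so that change in calcification score is primary and change in pulse wave velocity is secondary, and align the Summary with 7.1.1 and 7.1.2.

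The cost is rewording of section 9 and the Summary. No new data or visits are needed. If the multinomial model were kept as primary instead, the calculation in 4.4 would have to be redone for it.

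### Sections 4.4 and 9.1 name conflicting models for the primary endpoint, and the stated 90% power belongs only to the continuous one

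*Protocol*

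**What the plan says.** The primary objective (section 2) is to compare progression of coronary calcification between treatment modalities. The main endpoint (section 7.1.1) is the change in calcification score.

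Section 4.4 names a continuous model: "The effects of the different modalities of renal replacement therapy on arterial calcification are analyzed with linear regression, after transformation of calcium scores". It sizes the study on that basis: "we can demonstrate an increase or decrease in calcification score of 15" per cent. The calculation calls for four groups of 22, and its error rates are given as follows: "with a type I error probability for a two sided test of 0.05 and a power of 0.90".

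Section 9.1 notes that the score is skewed and then states: "Progression of calcification score will be analyzed with multinomial logistic regression, dividing the coronary artery calcification score in three categories". It adds: "The same goes for pulse wave velocity of the aorta and iliac arteries". It gives no cut-points and does not make clear whether the score or its change is cut. A closing sentence says that the groups' scores will be compared by regression, without naming the type.

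Sections 9.2 and 9.3 use linear regression for change in calcification score and in pulse wave velocity, and 9.2 corrects for the initial calcification score. Their explanatory variables are demographic, mineral-metabolism, inflammation and inhibitor measures. Treatment modality is not among them, and both sections list change in score as a secondary outcome.

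**The concern.** The sample size and the analysis section do not describe the same analysis. Section 4.4 relies on a continuous outcome. Section 9.1 cuts it into three classes and fits a model that ignores their order. Patients far apart within a class then count as equal, and each comparison of two modalities uses 2 degrees of freedom instead of 1. Pulse wave velocity, also continuous, is treated in the same way.

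Two things are at stake. If the three-category model is the primary comparison, the stated power does not apply to it. And while both models stand, with cut-points open, the choice between them could be made after the data are seen.

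**Working it through.** **Inputs, all from section 4.4.** Mean: "coronary calcification score in ESRD patients is 2370"; SD 352; difference 15% of the mean, 0.15 × 2370 = 355.5; two-sided alpha 0.05; power 0.90; 22 completers per group. The formula legend prints S = 3.52, but that would give 2 × (1.96 + 1.28)² × 3.52 / 355.5 = 0.2 patients, so 352 must be the value used.

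**Step 1: reproduce the plan's figure.**
- Formula as printed, SD 352: 2 × (1.96 + 1.28)² × 352 / 355.5 = 20.8, so 21.
- Standard two-means formula: 2 × (1.96 + 1.28)² × (352 / 355.5)² = 20.6, so 21.
- Standardised effect: 355.5 / 352 = 1.01 SD.
- Power at 22 per group: 91.8% (normal approximation), 90.5% (noncentral t).

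The planned 22 is therefore consistent with a continuous comparison of two groups.

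**Step 2: same effect and numbers, three categories.** Simulated normal outcomes, 22 versus 22, difference 1.01 SD, cut at pooled tertiles. That leaves 44/3 ≈ 15 patients per class, or about 7 per class per group.

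| Test | Power |
|---|---|
| Continuous t-test | 90.5% |
| Ordered test on three classes, 1 df | 82% |
| Multinomial likelihood ratio, 2 df | 73.4% (40,000 runs); 73.9% (20,000 runs) |
| Pearson chi-square, 2 df | 72.6% (40,000 runs); 73.0% (20,000 runs) |

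The likelihood-ratio test has a type I error of about 5.8–6.0% here, so its power is if anything flattered. A continuous test reaches 73% with 14 per group, so under these assumptions the cut costs the information of about 22 − 14 = 8 patients per group.

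**Step 3: vary the cut-points, since 9.1 gives none.** Likelihood-ratio power at 22 per group, cuts in SD units from the mean of the lower group:

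| Cuts | Power |
|---|---|
| 0 and 1 | 76.8% |
| −0.67 and 0.67 | 76.9% |
| 0 and 2 | 74.3% |
| −1 and 0 | 68.6% |
| −1.5 and 1.5 | 56.6% |

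Three further pairs gave 64–80%. The overall range is roughly 57–80%, and no pair tried came near 90%.

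**Step 4: all four groups together.** With 22 per group the result depends on the pattern of means.

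| Means (d = 1.01 SD) | ANOVA, 3 df | Multinomial, 6 df |
|---|---|---|
| 0, 0, d, d | 98.3% | 90.3% |
| 0, d, d, d | 93.5% | 77.0% |
| 0, d/2, d/2, d | 79.2% | 58.0% |

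The categorical test is weaker in every pattern.

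**The case against.** A reader might infer that the multinomial model is the planned analysis and that the trial therefore has only 74% power. The protocol does not support that.

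- **Which model is planned is unsettled.** Section 4.4 itself names linear regression for the modality effects. The multinomial sentence stands under a heading on descriptive statistics and does not mention modality. The sentence in 9.1 on comparing groups leaves the type of regression open. This objection stands, and it is why the finding is a conflict between sections and not a known shortfall. Sections 9.2 and 9.3 do not resolve the conflict, because their linear models concern risk factors.
- **The 74% is conditional.** It needs tertile cuts, a pairwise 2-df test, normal data and exactly 22 completers. The SD of 352 is that of the score level on its original scale; the protocol gives none for the change or for the transformed score. Hence neither 90% nor 74% is the power for the stated endpoint. This stands too, and 74% should not be written into 4.4.
- **More than 22 might complete.** The Summary allows 25% loss, and 40–55 are enrolled: 40 × 0.75 = 30 and 55 × 0.75 ≈ 41. Multinomial power would then be about 87–96%. But 4.4 lets enrolment vary with dropout, "aiming to obtain complete study data in 22 patients per group", so 22 is the number to which the 90% is tied. At 30 and 41 the continuous test would have 97.0% and 99.5%.
- **Skewness might justify classes.** A categorical analysis is not in itself an error. But 4.4 already deals with skewness by transformation, and 9.1 gives no reason specific to pulse wave velocity.

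**Conclusion.** The conflict is real and concerns the primary endpoint: the protocol names two incompatible models for it, and the stated power fits only one. If the three-category model is the primary modality comparison, the 90% does not carry over. On the plan's own effect with 22 per group, power is about 74% with tertiles and roughly 57–80% at other cut-points, against 90.5% for the continuous test. The direction of the loss held for every cut-point pair and pattern of means examined. Its exact size rests on the assumptions listed above.

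**What to change.** In 9.1, name the linear regression of 4.4 as the single primary analysis of progression by modality: transformed scale, adjusted for the initial calcification score as 9.2 already does. Analyse change in pulse wave velocity continuously as well. Keep the three classes as descriptive, or as a secondary analysis with an ordinal model.

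If the multinomial model is to be primary, fix its cut-points in advance, state whether score or change is cut, and recalculate the power in 4.4 for that model in place of the 90%.

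The cost of the first option is one paragraph, with no new data or patients. The downside is that the class-based odds ratios become descriptive or secondary.

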**“Intervention” (different modalities of renal replacement therapy, chosen by the patient, are observed):**

Group A: treatment with frequent nocturnal hemodialysis;

Group B: treatment with renal transplantation;

Group C: continuous treatment with hemodialysis;

Group D: continuous treatment with peritoneal dialysis.

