## **2. OBJECTIVES**

### **Primary objective:**

1. To assess whether frequent nocturnal hemodialysis and renal transplantation are associated with less progression of coronary artery calcifications, in comparison with conventional 3-times/week hemodialysis and with peritoneal dialysis.

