## **4. STUDY POPULATION**

### **4.1 Population**

The study populations consists of 4 cohorts of patients: patients who start with frequent nocturnal hemodialysis, patients who receive a renal transplant and 2 control groups treated with hemodialysis and with peritoneal dialysis. The study is sponsored by Dianet Dialysis Centers, while all research activities take place in University Medical Center Utrecht. Patients were screened at their local treatment facility (Dialysecentrum Groningen, Groningen; Dialysecentrum Diapriya, Amsterdam; VU medisch centrum, Amsterdam; Meander Medisch Centrum, Amersfoort; Rijnstate Ziekenhuis, Arnhem; Sint Antoniusziekenhuis, Nieuwegein; Stichting Dianet Dialysecentra, Utrecht and Amsterdam; and University Medical Center Utrecht, Utrecht), and if interested in the study, subsequently referred to University Medical Center Utrecht for study participation.

- 40 patients who start treatment with frequent nocturnal hemodialysis are asked to participate in the study;
  - 40 patients who receive a renal transplant, after having been treated with hemo- or peritoneal dialysis, are asked to participate in the study;
  - 40 patients who are treated with conventional hemodialysis are asked to participate; in order to enhance similarity between groups only hemodialysis patients are recruited that are or could be eligible to be on the waiting list for renal transplantation;
  - 40 patients who are treated with peritoneal dialysis are asked to participate; in order to enhance similarity between groups only peritoneal dialysis patients are recruited that are or could be eligible to be on the waiting list for renal transplantation.
- Groups will be matched according to age, sex, presence of diabetes mellitus and duration of dialysis, in order to minimize between-group differences to 25% regarding these factors.

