### **9.3 Multivariate analysis**

The effects of age, gender, body weight, blood pressure, medication, hemoglobin, lipids, quality-of-life, performance status and medication on the relation between each independent variable (demographic data, calcium-phosphate parameters, inflammation markers and calcification inhibitors), and primary outcomes will be determined with multivariate linear regression analysis. The effects of age, gender, body weight, blood pressure, medication, hemoglobin, lipids, quality-of-life, performance status and medication on the relationship between these independent variables and secondary outcomes (change in coronary calcifications score, change in pulse wave velocity) will be determined with multivariate linear regression analysis.

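### The initial calcium score is corrected for in the risk-factor regressions but not named in the primary comparison of self-chosen modalities, which leaves that contrast open to baseline imbalance

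*Protocol*

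**What the plan says.** The primary objective is "To assess whether frequent nocturnal hemodialysis and renal transplantation are associated with less progression of coronary artery calcifications" than conventional hemodialysis and peritoneal dialysis. The main endpoint (7.1.1) is "change in coronary artery calcification score". Allocation is not randomised; the Summary states that "different modalities of renal replacement therapy, chosen by the patient, are observed". The Summary and the investigations table in section 3 schedule the calcium-score CT at inclusion and at 1, 2 and 3 years.

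The modality comparison is described in two places:
- Section 4.4: modality effects "are analyzed with linear regression, after transformation of calcium scores". The transformation is not named.
- Section 9.1: "The calcification score of the different groups will be compared by regression analyses". The same section assigns progression to a three-category multinomial logistic regression.

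Neither place names a covariate.

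The only baseline correction is in 9.2: "the results will be corrected for initial calcification score". The independent variables there are demographic data, calcium-phosphate parameters, inflammation markers and calcification inhibitors. Modality is not among them. Section 9.3 then lists its adjustment variables, "The effects of age, gender, body weight, blood pressure, medication, hemoglobin, lipids, quality-of-life, performance status and medication on the relationship between these independent variables" and the outcomes, and the initial calcium score is not on the list.

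On balance between cohorts, 4.1 says: "Groups will be matched according to age, sex, presence of diabetes mellitus and duration of dialysis", aiming to keep differences on those factors to 25%.

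**The concern.** The protocol treats the initial score as something to correct for when it relates risk factors to progression, but does not carry that correction to the comparison the study exists to make. The need is greatest there, because the groups are self-selected and are not matched on calcium score. The nocturnal and transplant cohorts enter at the start of a new modality, while the two control cohorts are described as already under treatment, so different starting scores are plausible.

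Two things are at stake. The first is confounding: if progression depends on how much calcium is already present, a cohort that starts lower can appear to progress more slowly, or faster, with no modality effect at all. The second is precision: variation explained by the initial score stays in the error term of the primary contrast.

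**Working it through.** **Inputs from 4.4.** Mean score 2370, SD 352, target difference 15% (0.15 × 2370 = 355.5 points), two-sided alpha 0.05, power 0.90, 22 evaluable patients per group.

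**Reproducing the plan's figure.** n = 2(1.96 + 1.28)² × (352/355.5)² = 20.6, so 21 per group. An exact two-sample t-test with 22 per group has 90.5% power. The stated 22 is reproduced, taking SD as 352.

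**Assumptions that the document does not supply.** The yearly progression rate, the size of any baseline imbalance, and the correlation rho between baseline and follow-up score. All are illustrative below.

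**Imbalance under proportional growth.** Both groups progress 15% a year (no modality effect) and one group starts 10% lower. Growth over 3 years is 1.15³ − 1 = 0.5209.
- Raw scale: changes are 0.5209 × 2370 = 1234.5 and 0.9 × 1234.5 = 1111.0. The difference is 123 points, and 123/355.5 = 35% of the target.
- Square-root scale: the change in the first group is √2370 × (1.15^1.5 − 1) = 11.35. In the other it is 11.35 × √0.9 = 10.77. The difference is 0.58. The 15% target is √(2370 × 1.15) − √2370 = 3.52 units, so the share is 17%.
- Log scale: both groups change by 3 × ln 1.15, so the difference is zero.

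The raw-scale share for the same 10% imbalance is 11%, 22%, 35% or 49% at 5%, 10%, 15% or 20% a year.

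**The same imbalance under a linear model.** Suppose baseline and follow-up have equal SDs and the slope of follow-up on baseline is rho. A 10% imbalance is 237 points (237/352 = 0.67 SD).
- Unadjusted change: the spurious difference is (1 − rho) × 237, or 118.5, 71.1 and 23.7 points at rho 0.5, 0.7 and 0.9. That is 33%, 20% and 7% of the target. The sign is reversed: the group that starts lower shows the larger increase.
- Follow-up score alone: the difference is rho × 237, or 33%, 47% and 60% of the target at the same values, with the lower starter remaining lower.

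**Precision.** With score variance s², an unadjusted change has variance 2s²(1 − rho) and a baseline-adjusted analysis s²(1 − rho²). The ratio is (1 + rho)/2: 0.75, 0.85 and 0.95 at rho 0.5, 0.7 and 0.9. With 352 as the SD of the score, 22 per group and a 355.5-point difference, power for unadjusted against adjusted change is:

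| rho | unadjusted | adjusted |
|---|---|---|
| 0.5 | 90.5% | 96.5% |
| 0.7 | 98.8% | 99.6% |
| 0.9 | about 100% | about 100% |

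If the score itself were analysed without baseline, which the wording of 9.1 does not rule out, the variance ratio is 1 − rho²: 0.75, 0.51 and 0.19. These figures are for linear regression and do not carry over numerically to the multinomial model.

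**The case against.** The best defence is that 9.1 is silent rather than wrong: it names no covariates, so it excludes none, and a model's covariates are often left to an analysis plan. The 9.2 correction might also be meant more widely. This has weight, but the protocol did not leave baseline correction to a later document. It fixes it in 9.2, for analyses that do not list modality, and gives a covariate list without it in 9.3. A plan written to match would carry the gap into the primary contrast.

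Matching on age, sex, diabetes and dialysis duration gives some indirect balance, since section 1 links calcification to dialysis vintage in young hemodialysis patients. It is loose, and it is not balance on the score itself.

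Four stronger readings do not hold:
- A reader might apply the 25% tolerance in 4.1 to the calcium score and obtain a bias close to the whole target (309 of 355.5 points, 87%, on the raw scale at 15% a year). The tolerance covers the matching factors only, a 25% shift is about 1.7 of the stated SDs (592.5/352), and 4.4 specifies transformed scores.
- A reader might take the bias to be independent of any assumed correlation. That is true only under exact proportional growth; under the linear model both its size and its direction depend on the assumptions.
- A reader might count the 9.3 omission as harm to the modality contrast. The exposures in 9.3 are risk factors, so it affects those models only.
- A reader might call the reason given in 9.2 mistaken. It can be read coherently: if relative change does not depend on the starting score, absolute change does, hence the correction.

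**Conclusion.** The point stands as a gap in the primary analysis. An available baseline measurement, which the protocol itself corrects for elsewhere, is not named in the comparison of non-randomised groups. As written, that contrast is exposed to baseline imbalance and may lose precision.

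The document does not settle the size. For a 10% imbalance with equal 15% yearly progression it ranges from none (log change) through about 17% (square root) to about 35% (raw) of the target difference, and a linear model can reverse the sign. The precision gain over unadjusted change is material at rho near 0.5 or lower and small at high rho. Confounding is the more important half. Adjustment reduces it but does not guarantee its removal.

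**What to change.** 1. In 4.4 and 9.1, state that the modality regression includes the initial calcium score as a covariate, on the same transformed scale as the outcome, and name that transformation. Include the initial score in the multinomial model of progression as well.
2. Report the unadjusted change by modality as a sensitivity analysis. In self-chosen groups the adjusted and unadjusted results can differ, and readers should see both.
3. Separately, carry the 9.2 correction into the 9.3 risk-factor models by adding the initial score to the list there.
4. For change in pulse wave velocity, name baseline pulse wave velocity as the baseline covariate. At present no model names it; the only baseline correction stated is for calcium score.

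The cost is wording in 4.4 and 9.1 to 9.3. It needs no new data, visits or patients. A linear model spends one degree of freedom on the covariate, and the multinomial model spends one coefficient for each non-reference category.
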